## Abstract

**Background::**

Provision of education to a person with myocardial infarction and an active family member, who takes care of the patient can prevent or delay the onset of the disease. Telephone tracking is a very useful and inexpensive way to assess the patients’ needs and help them with their care problems. This clinical trial (interventional) protocol was conducted over the impact of family-based multimedia education based on the telephone tracking (tele-nursing) to improve the quality of life and self-efficacy in patients with myocardial infarction.

**Methods::**

Two phases are identified to design this study; the first phase includes designing a curriculum by investigating various studies and the panel of experts’ opinions. This phase will be conducted in the form of multimedia training and telephone contact. Multimedia training (including audio, video, image, and animation) over the patients’ lifestyle, nutrition, and care will be conducted through a one-day workshop in 2-3 hours for patients and one of their active family members. The active family member is defined as the primary caregiver, who spends more time with the patient. The educational course will be conducted at a coordinated date and time in the ward where the patients are hospitalized. The researcher will make telephone calls as the educational intervention and continue the follow-ups once a week for one month. The second phase of the intervention will contain a pre/post-test design along with application of Minnesota quality of life and Scherer general self-efficacy standard questionnaires in the intervention (with training) and control (without training) groups. The target participants will include all patients (and their active family members) admitted to CCUs of hospitals affiliated to Shahrekord University of Medical Sciences.

**Discussion::**

The present study provides useful data for designing a family-based multimedia educational intervention using the telephone-tracking method (tele-nursing) to improve the quality of life and self-efficacy in patients with myocardial infarction. It can also reduce their medical and treatment costs. The strategies of this program could be important and cost effective, and therefore we hope that the success of such a program is a step forward in improving cardiovascular patient’s health status.

**Highlights:**

## Background

Cardiovascular diseases are among the chronic illnesses and leading causes of death in the world. By 2020, cardiovascular diseases are estimated to be the first cause of disability on the world’s list of debilitating diseases [7]. Among the ischemic heart diseases, myocardial infarction is one of the most common and dangerous diseases in industrialized countries [1]. Myocardial infarction is ischemic necrosis of the cardiac myocytes that occurs due to a lack or loss of blood flow [6]. In the United States, about 5 million people develop cardiovascular diseases each year, which kills 285,000 people annually [13]. In Iran, cardiovascular diseases account for more than 46% of the total mortality rate, half of which is due to myocardial infarction [11]. Widespread expansion of the myocardial infarction causes complications such as congestive heart failure, acute pulmonary edema, cardiogenic shock, and mortality. It also imposes high care and treatment costs on patients [12]. Myocardial infarction is a non-infectious disorder that affects many aspects of life in patients and their family members, including their quality of life and self-efficacy [13]. In other words, chronic nature of the disease exacerbates the patients’ inability to meet their own needs. Failure to follow the health care diets is an important factor in increasing the odds of complications, mortality rates, and health care costs, while decreasing the quality of life and self-efficacy. Quality of life includes physical, psychological, and social dimensions as well as the patient’s personal feeling of health [3,10]. Provision of education to a person with myocardial infarction and an active family member, who takes care of the patient can prevent or delay the onset of the disease [2]. Family-based education involves active presence of a family member in identifying the patients’ needs and training them, since this type of education is based on the fact that occurrence of a disease in an individual enters all the family members into the disease cycle [14]. Multimedia software education, as one of the new educational methods, has affected all aspects of human life with the increasing advent of computers, information, and communication [5]. Telephone tracking is a very useful and inexpensive way to assess the patients’ needs and help them with their care problems [4]. Post-discharge telephone contact is helpful in identifying and modifying the care gaps that may occur after discharge [8]. This clinical trial (interventional) protocol was conducted over the impact of family-based multimedia education based on the telephone tracking (tele-nursing) to improve the quality of life and self-efficacy in patients with myocardial infarction.

## Methods/design

Two phases are identified to design this study; the first phase includes designing a curriculum by investigating various studies and the panel of experts’ opinions. This phase will be conducted in the form of multimedia training and telephone contact. Multimedia training (including audio, video, image, and animation) over the patients’ lifestyle, nutrition, and care will be conducted through a one-day workshop in 2–3 hours for patients and one of their active family members. The active family member is defined as the primary caregiver, who spends more time with the patient. The educational course will be conducted at a coordinated date and time in the ward where the patients are hospitalized. The researcher will make telephone calls as the educational intervention and continue the follow-ups once a week for one month. The time of telephone calls will be coordinated with the patients and their companions. The tele-communication contents will include verbal encouragement about health behaviors related to the educational and workshop contents. The research team will finalize the contents based on their priorities. The second phase of the intervention will contain a pre/post-test design along with application of Minnesota quality of life and Scherer general self-efficacy standard questionnaires in the intervention (with training) and control (without training) groups.

## Aim

In this study, we are seeking to design and implement a family-based multimedia educational intervention using the telephone-tracking method (tele-nursing) to improve the quality of life and self-efficacy in patients with myocardial infarction.

## Research hypotheses

Considering the main study purpose, some hypotheses will be considered according to the opinions provided by a panel of experts in cardiovascular diseases, health education, and nursing. Some hypotheses will be:

After the intervention, quality of life is better in the intervention group compared with the control group.

After the intervention, the general self-efficacy is higher in the intervention group than the control group.

## Phase I: designing the multimedia and tele-nursing software curriculum

At this phase, the intervention will be designed and the target audience will be identified based on the review of literature, similar studies, and information collected from questionnaires. After the panel of experts’ confirmation, the educational content prepared by researchers will be formulated based on three main themes and presented to the audience. The educational program consists of several sections.

**The first section** will include a training session with 10-member groups. The educational contents will be provided through multimedia training (audio, video, image, and animation) about patients’ lifestyle, nutrition, and care. This session will be conducted as a one-day workshop in 2–3 hours for patients and one of their active family members. The active family member is defined as the primary caregiver, who spends more time with the patient. The educational course will be conducted at a coordinated date and time in the ward where the patients are hospitalized.

**The second section** will be carried out using question/ answer format; at the end of the workshop, a session will be devoted to answer the participants’ questions about the educational content.

**In the third section**, the participants will be provided with educational files (in CD), so that they can review the covered contents at home.

**The fourth section** will be the telephone intervention. At the end of this session, the participants’ phone numbers will be collected and the researcher will contact them once a week for one month. Details of the educational intervention program are presented in ***Table 1***.

**Table 1 T1:** Multimedia educational intervention using the telephone-tracking method (tele-nursing).

PROGRAM	INTERVENTION CONTENT	PLACE AND METHOD OF PRESENTATION	AUDIENCE

Multimedia educational program	Introduction to exercise for patients with heart diseases; the type and level of activities Introduction to medication program, drug effects, medications’ side-effects and dosage in heart patients Introduction to diet and foods’ type, amount, and frequency in heart patients	In the form of a one-day workshop during 2–3 hours Using audio, video, image, and animation In the ward where the patients were hospitalized	Patients and their active family members

Question and answer	Questions and answers about the workshop’s content	Question/answer and discussion at the end of the workshop	Patients and their active family members

Presenting the educational file	Educational file in the form of CD	Providing the participants with the educational CD at the end of workshop	Patients and their active family members

Telephone-tracking (tele-nursing)	Verbal encouragement of the health-care behaviors related to the educational contents provided at the workshop or in the training CD	1month (once a week) The researcher coordinated the contact time with the patients and their family members	Patients and their active family members

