## Phase II: Implementation of educational intervention

In this step, a randomized controlled clinical trial will design to assess the efficacy of prepared protocol. Participants randomly will allocate into two groups. In one experimental group we will implement our designed protocol, and control group will not receive any intervention, but they follow as same as experimental group.

Participants will be selected based on the inclusion criteria and randomly divided into the intervention and control groups. After completing the written informed consent forms, the individuals will complete the pre-test questionnaires and the intervention group will receive the researcher-made educational package. During this time, the control group will not receive any education, but only the routine nursing care. At the post-test stage, that is one month after the intervention, all participants will be asked to complete the questionnaires and the collected data will be analyzed.

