## Study sample

The target participants will include all patients (and their active family members) admitted to CCUs of hospitals affiliated to Shahrekord University of Medical Sciences. The sample size was calculated as 60 (30 participants in each group) based on the previous studies and with respect to the type I error of 0.05 and the test power of 0.80.

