## Data analysis

We will apply X2 and independent T test to analysis our data by using SPSS version 21.

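### Workshop groups exist in the intervention arm only, but the named independent t test treats all 60 outcomes as independent; if the session ICC is above 0, the standard error is understated

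*Protocol article*

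**What the plan says.** All of this comes from the Protocol article.

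- **Delivery in the intervention arm** (Phase I section): the first part of the programme "will include a training session with 10-member groups". On attendance it says: "This session will be conducted as a one-day workshop in 2–3 hours for patients and one of their active family members". At the end of the workshop, "a session will be devoted to answer the participants’ questions about the educational content". A CD for home use and weekly telephone calls for one month follow.
- **Control arm** (Phase II section): "the control group will not receive any education, but only the routine nursing care".
- **Allocation** (Phase II section): "Participants randomly will allocate into two groups". Individuals are allocated, not workshop groups.
- **Analysis** (Data analysis section): "We will apply X2 and independent T test to analysis our data by using SPSS version 21".
- **Sample size** (Study sample section): "The sample size was calculated as 60 (30 participants in each group", followed by "with respect to the type I error of 0.05 and the test power of 0.80". The effect size and standard deviation are not given, only attributed to previous studies.

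Neither the analysis nor the sample size statement mentions workshop session, clustering or an ICC.

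**The concern.** Patients are randomised individually, but those in the intervention arm are then taught together while controls are not grouped at all. This is a partially nested design. Patients in one workshop share the occasion, the questions raised and the answers given, so their later quality-of-life and self-efficacy scores may be more alike than those of patients from different workshops.

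An independent t test has no term for this. With positive within-session correlation, the intervention-arm mean is less precise than the test assumes. The confidence interval is then too narrow and the false-positive rate rises above 0.05, which makes it easier to declare a benefit that is not there. With only 3 to 6 sessions, a few influential sessions could move the arm mean noticeably. Session membership is easy to record while the trial runs and may be hard to reconstruct afterwards.

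**Working it through.** **Inputs from the article.** 30 patients per arm; type I error 0.05; power 0.80; sessions of 10 members; controls ungrouped.

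**Assumptions.** The test is two-sided (the article does not say). The session ICC is 0.01, 0.05 or 0.10 (the article gives none). Patients per session, m, is 10 if members means patients (30/10 = 3 sessions), or 5 if the 10 members are patient-relative pairs (30/5 = 6 sessions). Total variance is equal in both arms.

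**Step 1: the plan's own figure.** The sample size of 60 cannot be reproduced, because no effect size or SD is stated. Solving backwards from 30 per arm by the normal approximation:

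d = (1.960 + 0.842) × √(2/30) = 0.723

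This is the standardised difference that 30 per arm detects with 80% power. It is inferred, not an effect the article states.

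**Step 2: variance of the difference.** The design effect applies to the intervention arm only: DE = 1 + (m − 1) × ICC. The true variance is SD² × (DE + 1)/30, whereas the t test uses about SD² × 2/30. The variance is therefore larger by the factor (DE + 1)/2, and the standard error by its square root.

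- m = 10, ICC 0.05: DE = 1 + 9 × 0.05 = 1.45; factor (1.45 + 1)/2 = 1.225, so the variance is 22.5% higher; √1.225 = 1.107.
- m = 5, ICC 0.05: DE = 1 + 4 × 0.05 = 1.20; factor (1.20 + 1)/2 = 1.10, so the variance is 10% higher; √1.10 = 1.049.

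**Step 3: power with the correct standard error.** Power = Φ(d/√((DE + 1)/30) − 1.960).

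- m = 10, ICC 0.05: 0.723/√(2.45/30) = 2.53; Φ(0.57) = 0.716, about 72%.
- m = 5, ICC 0.05: 0.723/√(2.20/30) = 2.67; Φ(0.71) = 0.762, about 76%.

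These treat the ICC as known, so they are optimistic for so few sessions.

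**Step 4: type I error of the planned test.** Simulation of 200,000 null trials per setting: normal outcomes, total variance 1 in each arm, a session effect with variance equal to the ICC in the intervention arm, and a t test on 58 df at two-sided 0.05.

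| Patients per session | ICC | DE | SE ratio | Type I error | Power |
|---|---|---|---|---|---|
| 10 (3 sessions) | 0 | 1.00 | 1.000 | 5.0% | 80% |
| 10 | 0.01 | 1.09 | 1.022 | 5.5% | 78% |
| 10 | 0.05 | 1.45 | 1.107 | 7.6% | 72% |
| 10 | 0.10 | 1.90 | 1.204 | 10.5% | 64% |
| 5 (6 sessions) | 0 | 1.00 | 1.000 | 5.0% | 80% |
| 5 | 0.01 | 1.04 | 1.010 | 5.2% | 79% |
| 5 | 0.05 | 1.20 | 1.049 | 6.1% | 76% |
| 5 | 0.10 | 1.40 | 1.095 | 7.4% | 73% |

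**Step 5: would modelling the sessions solve it?** Simulated with a session-mean Satterthwaite analysis, at the effect giving 80% power by the t distribution (d = 0.736):

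- 3 sessions of 10: power 68% at ICC 0 and 57% at ICC 0.05, with type I error still about 6%. The session variance estimate is zero or negative in 47% to 62% of trials over that ICC range.
- 6 sessions of 5: power 76% and 71%.

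By contrast, inflating the variance at a fixed ICC of 0.05 gives a type I error of 5.0% when that value is right.

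**The case against.** The strongest reply is that clustering here may be weak. The shared part is a single workshop of 2 to 3 hours built on standard audio-visual material. The CD is used at home and the telephone calls are arranged with each patient. The article describes one researcher making the calls, so no clustering by several therapists arises. Outcomes are self-reported one month after the intervention. All of this argues for a small ICC, and at 0.01 the inflation is negligible (5.2% to 5.5%). The 0.10 rows show the upper end of an assumed range and have no support in the text. This part of the objection stands. It limits the size of the problem but does not remove the shared session.

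A second reply is that the article is condensed and an adjustment or sensitivity analysis might sit in an analysis plan that is not shown. This stands only in part, because the article does name the test and that test assumes independence.

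A reader might go further and infer that the planned p values are certainly too small, or that the sample size is shown to have ignored clustering. The documents support neither. The first depends on an ICC they do not give. The second cannot be judged, because the effect size and SD behind the 60 are not reported and a fuller protocol might contain an allowance.

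**Conclusion.** The point holds in conditional form. Grouped delivery in one arm and a test that assumes independence are both stated in the article, and they do not fit together. For any positive session ICC the planned test understates the standard error and errs towards declaring benefit; at ICC 0 it is correct.

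Over the assumed ICC range of 0.01 to 0.10, type I error runs from 5.5% to 10.5% with 3 sessions of 10 patients and from 5.2% to 7.4% with 6 sessions of 5. The article does not say which session size applies, and the smaller one roughly halves the inflation. The power figures also rest on the back-solved effect of about 0.72 SD. The problem merits a planned safeguard; it does not by itself invalidate the trial.

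**What to change.** 1. State whether the 10 members are patients or patients plus relatives, and record the session each intervention patient attends.
2. Beside the planned t test, report for each outcome the between-arm difference with its confidence interval and p value, using SE = √(s²_I × DE/30 + s²_C/30), where s²_I and s²_C are the variances in the intervention and control arms and DE = 1 + (m − 1) × ICC. Do this at fixed ICCs of 0.01, 0.05 and 0.10, named before the data are seen.
3. Call a benefit robust only if it holds across that range.
4. A partially nested mixed model (session random effect in the intervention arm only, small-sample degrees of freedom) can be supportive. It should not be the sole main analysis with 3 to 6 sessions, because the ICC is poorly estimated and power drops sharply.

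The cost is one recorded variable, a short additional table and a somewhat wider interval: at ICC 0.05, about 11% wider with sessions of 10 patients or 5% with sessions of 5. Nothing in the delivery of the intervention has to change.

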## Sampling method

Random sampling’s method will apply to select the participants.

Participants will be divided into the intervention (receiving the training program) and control (not receiving the training program) groups according to the random number table.

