## Data collection method

### 1. Minnesota Quality of Life Questionnaire

This questionnaire was designed by Rector in 1984 to determine the impact of treatment on quality of life in patients with heart failure (30). This questionnaire is the most common tool used to assess the patients’ quality of life in research studies (31). The Minnesota Questionnaire assesses the patients’ perception from the heart failure effects on the physical, social, and psychological aspects of their lives. This scale contains 21 items dealing with the physical (N = 13), psychological (N = 4), and socio-economic (N = 4) aspects (32). Each question contains 6 criteria ranging from zero (the best situation) to five (the worst condition). The attainable scores can range from zero to 105; higher total scores indicate greater impact of the disease on the patients’ quality of life (i.e., lower quality of life). A change of 5 scores or more shows a significant improvement in severity of symptoms and quality of life. This questionnaire has had high reliability and validity compared to other similar questionnaires and achieved a Cronbach’s alpha of above 0.9 in all previous studies (33).

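### Ward-based group teaching and a take-home CD may expose individually randomised controls to the education, and the listed measurements would not show it

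*Protocol article*

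**What the plan says.** All references are to the protocol article.

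- **Where the teaching happens.** Under Phase I: "The educational course will be conducted at a coordinated date and time in the ward where the patients are hospitalized". The session lasts 2 to 3 hours, is run in groups of 10, uses audio, video, images and animation, includes an active family member, and ends with open questions.
- **What is handed out.** Table 1 lists "Providing the participants with the educational CD at the end of workshop". The CD is meant for review at home.
- **How participants are allocated.** Under Sampling method, participants go to the intervention or to the "control (not receiving the training program) groups according to the random number table". Study environment and population, and Study sample, draw everyone from the CCUs of the hospitals affiliated to one university. No allocation by ward, hospital or period is described.
- **What controls are meant to receive.** Under Phase II: "the control group will not receive any education, but only the routine nursing care".
- **Who can use the CD.** The inclusion criteria require computer access and the ability to use it of every participant, controls included.
- **What is measured.** The article lists the Minnesota quality-of-life and Sherer self-efficacy questionnaires, completed again one month after the intervention and compared with chi-square and independent t tests.

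**The concern.** The control condition is an absence of education, yet the article sets the teaching in a place that controls may share. Individual allocation within common CCUs means that a control patient and an intervention patient can be on the same ward at about the same time. Two routes of exposure follow from the stated delivery: seeing or hearing a long audiovisual group session with discussion, and borrowing or copying the CD. The second route is helped by the eligibility rule, which selects controls who can use such a CD, and by the month between intervention and post-test.

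If some controls learn from the material, their scores move towards those of the intervention arm and the observed difference understates the effect of the programme. With only the two questionnaires to look at, a null result would have two explanations, an ineffective programme or exposed controls, and the data would not separate them.

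**Working it through.** **Inputs**

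- From Study sample: 30 per arm, and "with respect to the type I error of 0.05 and the test power of 0.80".
- Not given: effect size, SD, or whether the test is one- or two-sided. The article says only that the size is "based on the previous studies". I assume a two-sided test.
- Assumed, because the documents give no figure: p, the share of controls exposed, and f, the fraction of the full effect that an exposed control gains.

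**Step 1. The plan's own figure.** The total of 60 cannot be reproduced forward without an effect size, so I solve backwards for the standardised difference d that gives 80% power with n = 30 per arm.

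- Normal approximation: d = (1.960 + 0.842) × √(2/30) = 0.723.
- Noncentral t, 58 degrees of freedom: d = 0.736.
- If the test were one-sided: 0.642 (normal) or 0.650 (t).

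The stated size therefore fits a two-sided design difference of about 0.72 to 0.74 SD. This is an inference; the article does not state it.

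**Step 2. Dilution.** With c = p × f and the SD unchanged, the expected difference falls from d to d × (1 − c). In the normal approximation:

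power = Φ( d(1 − c) × √(n/2) − 1.960 ), with √(30/2) = 3.873 and 0.7234 × 3.873 = 2.802.

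Example, c = 0.20: 2.802 × 0.80 − 1.960 = 0.281, and Φ(0.281) = 0.611.

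The noncentral t calculation from d = 0.736 agrees to within about 0.001.

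| Controls exposed (p) | Power, full effect (f = 1) | Power, half effect (f = 0.5) |
|---|---|---|
| 0% | 80% | 80% |
| 10% | 71% (c = 0.10) | 76% (c = 0.05) |
| 20% | 61% (c = 0.20) | 71% (c = 0.10) |
| 30% | 50% (c = 0.30) | 66% (c = 0.15) |

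**Step 3. The same loss in patients.** Required size grows by 1/(1 − c)². From 30 per arm: 30/0.81 = 37.0 at c = 0.10, 30/0.64 = 46.9 at c = 0.20, and 30/0.49 = 61.2 at c = 0.30, so 38, 47 and 62 per arm after rounding up.

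**Step 4. Which column is realistic.** The programme has four parts: workshop, question session, CD and weekly telephone calls for a month. Overhearing a session or borrowing a CD cannot deliver the calls, which are made to participants whose numbers were collected at the workshop. The f = 1 column is therefore the worst case at each exposure rate.

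**The case against.** The case on the other side has several parts.

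- **Controls are not stated to be present.** The article names several hospitals and does not say how many wards there are or whether the arms overlap in time. A reader might infer that controls are known to lie beside the session; the documents do not say so. This stands: shared wards are a likely consequence of the design, not a stated fact.
- **On the ward need not mean at the open bedside.** The session is scheduled in advance and could be held in a side room. This also stands. Lending or copying of the CD is likewise a possibility, not something described.
- **The article condenses a fuller protocol.** Instructions on sharing or a record of exposure may be there, so their absence here would not be a finding in itself. This stands for absence alone. But the article does commit to individual allocation, delivery on the ward and a handed-out CD, and it is this combination that works against an uneducated control arm.
- **The passages do not contradict each other.** One says where the intervention arm is taught, the other what controls are given. Agreed: there is tension between them, and no inconsistency of fact.
- **The power figures could be taken for the trial's own.** A reader might infer that it was planned on 0.74 SD, or that its power will be 50% to 71%. Neither is supported: the first is back-solved, and the second assumes exposure rates and full carry-over.
- **Dilution cannot manufacture a benefit.** Correct, and it limits the harm to missed or understated effects.

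**Conclusion.** The point holds as a risk created by the stated delivery. Controls may share wards with intervention patients and be exposed to the material, contrary to the intended control condition, and the measurements listed would not reveal it. The bias is towards no difference. A positive result would stand, though the effect might be understated; a null result could not be told apart from contamination.

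The size cannot be computed from the documents. As a sensitivity range for 10% to 30% of controls exposed, power would be at worst about 71% to 50% with full carry-over, and about 76% to 66% with half. These figures rest on a two-sided test at 0.05, a design difference back-solved from 30 per arm and 80% power, an unchanged SD, and assumed values of exposure and carry-over. The documents do not show that contamination will occur, and the point gives no reason to abandon individual randomisation. It is a cheap improvement, not a demonstrated defect.

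**What to change.** Keep individual randomisation and make three small changes:

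1. In Phase I and Table 1, specify that the session is held, where feasible for inpatients, in a room of the ward or hospital out of sight and hearing of control patients.
2. Ask intervention patients and their families not to share or copy the CD until the post-test is finished.
3. Add one post-test item, in both arms, asking whether the participant saw the workshop or the CD. Report the share by arm beside the as-randomised result, which remains the main comparison.

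The cost is a small logistical burden: finding a suitable room, one instruction and one question. Whether CCU inpatients can be moved for 2 to 3 hours is for the sites to judge, so the first change must stay conditional; the other two do not depend on it. No extra patients are needed. The limit is that the exposure item reveals contamination but does not remove it.
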